## Abstract

**Question:**

Can inaudible high-frequency sounds augment the efficacy of cognitive behavioral therapy for anhedonia?

**Findings:**

This trial protocol describes a placebo-controlled, randomized clinical pilot study testing the augmentation effect of inaudible high-frequency sounds on positive valence system–focused cognitive behavioral therapy among patients with clinically significant anhedonia and depression. The sound presentation system is designed to optimize exposure to inaudible high-frequency sounds during face-to-face cognitive behavioral therapy sessions.

**Meaning:**

The preliminary results of this pilot study could contribute to the design of confirmatory randomized clinical trials that will examine the augmentation effect of inaudible high-frequency sounds on the treatment of anhedonia.

## Introduction

Mental disorders cause devastating effects at both the individual and societal level. Among these disorders, major depressive disorder is the leading cause of the global disease burden.^1^ According to treatment guidelines and systematic reviews, cognitive behavioral therapy (CBT) is recommended for patients with depression who experience moderate to severe symptoms.^2^ Nevertheless, the therapies available to treat depression can be improved. A 2010 meta-analysis^3^ showed that the standardized mean effect size of CBT for depression was low (*d* = 0.22) in a high-quality randomized clinical trial. A 2008 meta-analysis^4^ reported that 50% of patients relapsed after completing CBT, and 50% of those who did respond to treatment relapsed within 2 years. To overcome these situations, translational research bridging neuroscience and CBT has focused on developing novel CBT approaches or techniques that augment traditional CBT.^5,6,7^ Among them, we focused on the following 2 noninvasive interventions: (1) positive valence system–focused CBT (PoCot) and (2) inaudible high-frequency sounds. These interventions target the common neurological underpinnings of anhedonia.

Anhedonia, 1 of 2 cardinal depression symptoms, is known to be less responsive to both CBT and pharmacotherapy than other depressive symptoms.^8,9^ Anhedonia is the loss of interest or pleasure associated with deficits in reward-related brain circuity.^10,11,12^ Dysfunction of this circuity includes blunted activation of the striatal regions and orbitofrontal cortex as well as blunted mesolimbic dopamine pathways.^11,13^ It has been suggested that major depressive disorder is characterized by an underestimation of reinforcements received, a reduced expectation of future rewards, less frequent endorsement and recall of positive traits in self-referential tasks, a diminished ability to modulate behavior as a function of reinforcement history, a reduced willingness to make efforts to gain rewards, and an inability to couple the hedonic impact of stimuli and reward assumption.^13^ According to Research Domain Criteria,^14^ anhedonia reflects disturbances of the positive valence system.^15,16^

The positive valence system has been largely neglected in traditional psychotherapeutic techniques, including CBT.^17^ Findings in the field of neuroscience have led to the development of a CBT approach that directly targets the positive valence system; studies have demonstrated the efficacy of this novel CBT approach.^18,19,20,21^ It requires patients with depression to engage in activities that are designed to enhance the subconstructs of positive valence systems (eg, behavioral activation for improving motivation, positive awareness training for improving sensitivity to rewarding stimuli, and savoring training for the loss of pleasure). Craske et al^22^ reported that this positive affect training was more effective for improving anhedonia (ie, increasing positive affect) and reducing a patient’s negative affect and suicidality than more conventional types of CBT (ie, CBT approaches targeting negative affect). Therefore, we believe that the PoCot approach may improve the efficacy of traditional CBT approaches for anhedonia.

The second approach that targets the positive valence system focuses on the hypersonic effect of inaudible high-frequency sounds. Hypersonic effect refers to the whole-body response following exposure to inaudible high-frequency sounds via deep brain activity activation, including reward-related neural circuitry.^23^ Using inaudible high-frequency sounds recorded in a tropical rain forest, our research group previously demonstrated this phenomenon using various noninvasive brain function imaging and physiological measures.^23^ For example, our positron emission tomography study^23^ with healthy control participants demonstrated that inaudible high-frequency sounds, compared with high-cut placebo sounds, increased blood flow in the reward circuit and affected related circuity, including monoaminergic projections distributed across the brain stem, thalamus, and prefrontal region.

Inaudible high-frequency sounds have also been shown to produce higher electroencephalographic (EEG) alpha-band (ie, 8-13 Hz) power.^23^ In addition, in a 2013 study with healthy controls,^24^ simultaneous EEG and functional magnetic resonance image acquisitions indicated that the slow fluctuation component of EEG alpha power was positively associated with blood oxygen level–dependent signal changes in the brain stem, medial thalamus, and anterior cingulate cortex, all of which can be considered part of the reward-related neural circuitry. This observation again suggested that the changes in EEG alpha power induced by inaudible high-frequency sounds may correspond to the activation of reward-related circuitry. Moreover, inaudible high-frequency sounds have been reported to promote approach behavior^25^; this may reflect reward-system activation (eg, better subjective mood or choosing higher levels of sound volume). Overall, inaudible high-frequency sounds have been shown to robustly enhance the subjective experience of sound quality and comfort and to promote approach behavior. Regarding the underlying physiological mechanisms, our previous study^26^ demonstrated that the hypersonic effect may be induced not through the auditory system but through the body’s surface. Although the underlying physiological mechanisms remain unclear, the overall accumulated evidence robustly suggests that inaudible high-frequency sounds enhance the reward system.

We hypothesized that the combination of the PoCot approach and inaudible high-frequency sounds would have a synergistic effect on anhedonia. Although, to our knowledge, no previous direct findings support this idea, PoCot is designed to enhance the brain reward circuity,^18,20^ while inaudible high-frequency sounds increase blood flow.^23^ In addition, reward circuity activation via inaudible high-frequency sounds leads to a relaxed attentional state.^27^ Considering that CBT is a learning process^28^ and positive emotions enhance the learning process,^29^ it is expected that a positive emotional state induced by inaudible high-frequency sounds will facilitate the learning process in CBT. Furthermore, inaudible high-frequency sounds are expected to enhance learning via EEG alpha-band power activation. The alpha-band frequency range inhibits activity in task-irrelevant brain regions, enabling effective task-irrelevant disengagement for information processing.^30^ In addition, inhibiting task-irrelevant memories coupled with alpha-band activity is believed to enhance semantic orientation, allowing individuals “to selectively access stored information that represents the meaning of sensory information and ‘higher order information,’ such as language, mathematics, and geography.”^31^^(p613)^ Hence, we expect that inaudible high-frequency sounds will augment the learning process of CBT via an induced relaxed attentional state and alpha band brain activity.

## Methods

### Trial Design

This trial was designed with an individual-level allocation with a 1:1 ratio. It is an exploratory, randomized clinical superiority phase II trial. Therapists, patients, and evaluators will be masked to allocation. The trial protocol appears in Supplement 1. This report followed the Standard Protocol Items: Recommendations for Interventional Trials (SPIRIT) reporting guideline.

### Study Setting

This study will be conducted at the National Center of Neurology and Psychiatry (NCNP) Hospital in Tokyo, Japan. Patients who are nonresponsive to primary care in their local clinic or hospital are commonly referred to the NCNP Hospital. A detailed description of the setting appears elsewhere.^32^

### Eligibility Criteria

The inclusion criteria are as follows: patient (1) has anhedonia symptoms (Snaith-Hamilton Pleasure Scale [SHAPS] score ≥20), (2) has mild to severe depressive symptoms (GRID-Hamilton depression rating scale score ≥8),^33^ and (3) is aged 18 years or older. The exclusion criteria are as follows: patient has (1) current psychotic disorder, (2) current manic episodes, (3) severe substance use disorder, (4) serious suicidal ideation, (5) severe or unstable physical disorder or major cognitive deficit, and (6) other problems that may present serious obstacles regarding CBT. Exclusion criteria, except for items 5 and 6, will be assessed using the Mini-International Neuropsychiatric Interview version 7.0.2.^34^

### Interventions

#### Positive Valence System–Focused CBT

Both the intervention and control group will participate in PoCot, which will be conducted in a face-to-face, individualized format. Weekly sessions lasting 50 to 60 minutes will be conducted in a room with sound equipment. This intervention was developed using CBT advances that focus on the positive valence system,^18,19,20,21^ positive psychological interventions,^35^ positive emotion regulation interventions,^36^ traditional Japanese psychotherapy that emphasizes positive affect and reward,^37,38^ and findings from neuroscience and emotion research mentioned in the introduction.^29,39^ Biological and theoretical background information and details of the intervention are provided in the eAppendix and eTable in Supplement 2.

Early PoCot sessions will include psychoeducation that emphasizes the importance of the positive valence system for anhedonia treatment. The participants will then begin to practice savoring positive sensations and emotions and attentively monitoring positive events in daily life. Participants will be asked to identify thoughts that interrupt their mindful acceptance of positive sensations and emotions and to examine alternative thoughts. In parallel, the participants will be encouraged to identify their strengths and try to use them in daily life. To help identify strengths, participants will be asked to identify past positive memories.

The focus of the program will then gradually shift from enhancing the patient’s acceptance of short-term positive experiences (ie, short-term reward) to engaging longer-term, goal-directed, and more effortful behavior. Psychoeducation on the temporal discounting of rewards in anhedonia will be provided. The participants will be asked to identify longer-term goals or values in their lives. These goals will then be divided into smaller steps, and patients will be encouraged to engage in easier behaviors. Furthermore, patients will be asked to monitor events they are grateful for in daily life and to practice receiving and providing compliments to enhance positive interpersonal experiences. In the final session, participants will review the skills they acquired during the program and discuss how to maintain a positive lifestyle.

#### Sound Material and Presentation System for Inaudible High-Frequency and Placebo Sounds

The intervention group will be exposed to inaudible high-frequency sounds during PoCot sessions. Rainforest sounds, a natural sound source containing the richest amount of high frequencies with a conspicuously fluctuating structure, were chosen as the sound source for this trial. Sounds containing inaudible high-frequency components (HFCs), referred to as *full-range sounds*, were recorded in the rainforest of Borneo from 2004 to 2009 using a high-speed, 1-bit coding signal processor in a direct stream digital format at a sampling frequency of 5.6 MHz. The electrical signal contains a wealth of HFCs (ie, >100 kHz). The sounds include animal and bird calls, insects chirping, and wind. The track is 47 minutes long and will be presented on repeat.

We selected PoCot without inaudible high-frequency sounds (ie, placebo sounds) as the comparator because previous studies successfully used placebo sounds as a comparator.^23,26^ There was almost no difference in the subjective experience of sound quality between inaudible high-frequency sounds and the placebo sounds. To generate placebo sounds, the inaudible HFCs were excluded from the original sound material using a low-pass filter (digital finite impulse response filter; cutoff frequency, 27 kHz; allowable passband ripple, 0.5 dB; stopband, 28 kHz-150 dB) using the MATLAB signal processing toolbox (MathWorks, Inc).

The level of audible sounds should not disturb conversations during PoCot, and the preferred sound level may vary depending on individual participants and therapists. Conversely, the inaudible HFCs should be presented equally to all participants in the intervention group. To this end, we constructed an original sound presentation system whereby the sound source signals recorded in a digital audio player (MR-2000S; KORG) can be divided into 2 pathways by a splitter with an independent volume control for each pathway (Behringer MX882; Behringer Music Group) (Figure 1). Using this presentation system, the fixed level of HFCs can be determined regardless of the audible low-frequency component level.

**Figure 1. zoi190599f1:**
[figure not shown]
Sound Presentation System In the higher pathway, full-range sound (FRS) sources, which contain high-frequency components (HFCs) and low-frequency components (LFCs), are sent to wide-range, powered speakers (Oohashi Monitor Op. 7; Action Research Co) through a volume controller. In the lower pathway, HFCs are extracted from the sound source after passing through an independent volume controller using Butterworth Bessel high-pass filters (cutoff frequency, 40 kHz, −48 dB per octave) and sent to super-tweeters (PT-R9; Pioneer Co) through a power amplifier (Cerenate; Fidelix). Audible LFCs and HFCs are transmitted via the first pathway, while the inaudible HFCs are presented via the second pathway.

As the study will use a short-term intervention, all participants will be asked to participate in all 8 sessions. If participants must cancel a scheduled session, an alternative date will be scheduled immediately. Participants will be exposed to their assigned audio track during the entire PoCot session. The sound volume will be set in advance at approximately 55 dB. Participants will sit 2 m away from 2 fixed speakers and tweeters (eFigure 1 and eFigure 2 in Supplement 2).

### Objectives

#### Primary Objective

The primary objective of this trial is to compare the efficacy of PoCot with in-session exposure to inaudible high-frequency sounds vs PoCot with in-session exposure to placebo sounds on anhedonia symptoms. Anhedonia symptoms will be assessed by 44 patients who have been diagnosed with clinically significant anhedonia symptoms using the SHAPS.^40^

#### Secondary Objectives

The key secondary objective is to evaluate the severity of anhedonia symptoms using the clinician-rated version of the SHAPS (SHAPS-C).^41^ Additional outcome variables, including depression, positive emotion, negative emotion, satisfaction with life, and psychological well-being will also be assessed. In addition, a moderation and mediation analysis will be performed using the following 2 measures, which are relevant to the treatment mechanism: (1) perception of environmental rewards and (2) effort-based decision-making. Perception of environmental rewards will be assessed by the Environmental Reward Observation Scale.^42^ Based on behavioral theory, this brief scale was developed to subjectively evaluate environmental reward as an important treatment mediator of traditional and new behavioral activation techniques. Effort-based decision-making will be assessed using the Effort-Expenditure for Rewards Task.^43^ Also, the relationship between the treatment process (eg, homework adherence) and outcomes will be examined.

### Participant Timeline

The timeline is depicted in Figure 2. During the study period, all patients will continue treatment as usual.

**Figure 2. zoi190599f2:**
[figure not shown]
Study Flow Diagram

### Sample Size

It is difficult to estimate the necessary sample size because previous studies have not directly tested our hypothesis. Among the most studied augmentation strategies of CBT is the effect of D-cycloserine on CBT for anxiety disorders; a meta-analysis^44^ reported that the standardized effect size of the augmentation on various outcomes ranged from 0.07 to 0.58. Based on this range, we conservatively selected a relatively low effect size to assess the augmentation effect of inaudible high-frequency sounds on CBT efficacy. We set a standardized effect size of 0.2 to 0.3 as the clinically significant minimum level. To detect the effect size, a sample size of 344 to 786 participants is needed for the main trial. For this pilot trial, we used the approach that was proposed specifically for calculating sample size for a randomized clinical pilot trial.^45^ Using this strategy, 32 to 72 individuals are needed. Hence, a sample size of 40 is sufficient for this trial. Assuming a 12% dropout rate, we included a total of 44 patients. Before starting the main pilot trial, we will conduct an external preliminary trial on 3 patients to examine the trial’s feasibility.

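### Sample Size: 40 participants meet the article's own pilot requirement only for effects of about 0.27 or larger, not down to the stated 0.2

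*Protocol article*

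**What the plan says.** The calculation stands in one paragraph of the protocol article (Methods, Sample Size). The target is a range: "We set a standardized effect size of 0.2 to 0.3 as the clinically significant minimum level". Two size ranges follow from it. For the later confirmatory trial: "To detect the effect size, a sample size of 344 to 786 participants is needed for the main trial". For the pilot, by a published method for sizing randomized pilots, the range and the conclusion come together: "Using this strategy, 32 to 72 individuals are needed. Hence, a sample size of 40 is sufficient for this trial". The paragraph then adds "Assuming a 12% dropout rate, we included a total of 44 patients". Trial Design gives 1:1 allocation, so 40 means 20 per arm.

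The article gives no reason for choosing 40 within the range and does not narrow the target effect to fit it. It describes its choice of a low effect size as a conservative one. Under Limitations it says that the sample size calculation was designed to show whether a larger trial is appropriate, and it asks for cautious interpretation.

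**The concern.** A required sample size falls as the effect to be covered grows. A range of 32 to 72 attached to effects of 0.2 to 0.3 is therefore two answers to two questions, not a band in which any number will do. A total of 40 lies near the large-effect end, yet the sentence that declares it sufficient carries no restriction.

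At stake is how a null or small result will be read. The pilot exists to inform the decision on a larger trial. If readers take the sentence at face value, they may treat a null result as informative about the whole 0.2 to 0.3 range. By the article's own figures the sample was not sized for the lower part of that range, which is also the part that would call for the largest main trial (786 against 344).

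**Working it through.** **Inputs from the article:** effects 0.2 and 0.3; pilot totals 32 and 72; main-trial totals 344 and 786; chosen pilot total 40; 44 enrolled; 12% dropout; 1:1 allocation; two-sided 5% tests (Statistical Analysis).

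**Inferred or assumed:** the article does not state the pilot method's confidence level. A one-sided 80% level is inferred because it reproduces both pilot figures. Power of 80% for the main trial is an assumption.

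**1. Reproduce the pilot figures.** Let the half-width of a one-sided 80% limit equal d, so that n per arm = 2(z/d)² with z = 0.8416.
- d = 0.2: 2(0.8416/0.2)² = 35.4, so 36 per arm, 72 in total.
- d = 0.3: 2(0.8416/0.3)² = 15.7, so 16 per arm, 32 in total.

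Both match exactly. A one-sided 90% level would give 166 and 74, and a 95% level 272 and 122, so neither fits. This fixes the pairing of 72 with 0.2 and 32 with 0.3. The ratios to the main-trial sizes agree with it: 72/786 = 9.2% and 32/344 = 9.3%.

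**2. Smallest effect for which 40 meets the requirement.**
- By the formula: d = 0.8416 × √(2/20) = 0.266.
- Without the inferred level, since the required N is proportional to 1/d²: 0.2 × √(72/40) = 0.268, and 0.3 × √(32/40) = 0.268.

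The answer of about 0.27 therefore does not depend on the inferred 80%.

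**3. After dropout.** 44 × 0.88 = 38.7 evaluable. The formula gives 2 × 0.8416/√38.72 = 0.271, and scaling gives 0.2 × √(72/38.72) = 0.273. If all 44 were evaluable, the values would be 0.254 and 0.256.

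**4. Size of the gap at 0.2.** 40/72 = 56%, or 32 participants short. The implied one-sided confidence with 40 is Φ(d√40/2):
- d = 0.2: Φ(0.632) = 0.74, against the 0.80 that the method appears to aim for.
- d = 0.3: Φ(0.949) = 0.83.

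**5. Effect of baseline adjustment.** With a baseline correlation r, the limit shrinks by √(1 − r²). The article gives no r. As an illustration, r = 0.5 gives 0.266 × 0.866 = 0.23. Reaching 0.2 needs √(1 − r²) = 0.2/0.266 = 0.75, that is, r of about 0.66.

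**6. Side check on the main-trial range.** n per arm = 2(1.960 + 0.8416)²/d² gives 393 per arm (786 in total) at 0.2, which matches. At 0.3 it gives 175 per arm (350 in total), against the stated 344.

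**The case against.** The strongest reply is that nothing in the pilot figures is miscalculated. Both 32 and 72 are reproducible, 40 lies between them, and it exceeds what the method asks for at 0.3, which is one end of the stated minimum range. The article never says in terms that 40 serves every point of the range. The trial is labelled exploratory, and Limitations already asks for caution. The primary model adjusts for baseline SHAPS, so the unadjusted gap overstates the shortfall by an unknown amount. The full protocol may also give the reason for 40.

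Much of this stands, and it limits the point to an unqualified conclusion drawn from correct figures. It does not remove the point. The target is given as a range, the conclusion follows with no restriction, and neither the exploratory label nor the general caution tells the reader that the lower part of the range is not met. No gain from baseline adjustment is claimed in the calculation.

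A reader might infer more: that the pilot cannot rule out an effect of 0.2. The documents do not support that. The rule of excluding an effect by an 80% limit is itself inferred and appears nowhere in the article. Even under that rule, the limit of 0.266 applies only when the observed difference is exactly zero. With 20 per arm the standard error is √(2/20) = 0.316, so an observed effect below 0.2 − 0.266 = −0.066 brings the upper limit under 0.2. If the true effect is zero, this happens with probability Φ(−0.066/0.316), about 0.42, against about 0.50 with 72 participants. The pilot can exclude 0.2, only less often.

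**Conclusion.** The point holds as a moderate one about wording. By the article's own figures, 40 participants meet the stated requirement for a minimum effect of 0.3 and for effects down to about 0.27. They do not meet it for 0.2, where the sample is 56% of the stated need and the implied one-sided confidence is about 74% instead of 80%. The threshold of about 0.27 rests only on the article's 32 and 72 and on 1/d² scaling. The 74% rests in addition on the inferred one-sided 80% level. Both are before baseline adjustment, which could narrow the gap by an amount that the article gives no means to calculate.

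It would be wrong to take 0.27 as a new clinical threshold. It is only what the chosen N happens to cover, and an importance threshold should not be derived from a sample size. The difference between 344 and 350 is under 2%, depends on the assumed 80% power, and has no bearing on 32, 72 or 40.

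**What to change.** Replace the sufficiency sentence in Sample Size with:

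> A sample of 40 meets the requirement for a minimum effect of 0.3 (32 needed) and covers effects down to about 0.27 without baseline adjustment; it does not meet the requirement of 72 for an effect of 0.2.

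Add, there or under Limitations, that a null pilot result will not by itself be read as excluding effects of 0.2 to about 0.27. Do not write that 0.2 cannot be excluded, and do not adopt 0.27 as the minimum important effect. In the same edit, recompute 344, or state the power and method that give it.

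The cost is a few sentences of text. No patients are added and no analysis changes; the stated capability of the pilot becomes slightly narrower.

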#### Statistical Analysis

##### Outcome Analysis

A mixed model for repeated-measures analysis will be conducted to analyze the primary outcome. The dependent variables in this model will be the participants’ SHAPS scores, assessed during 8 visits from weeks 1 to 11 (ie, intervention period) and at week 12 (ie, postintervention period). The fixed effects will be allocation, visit, allocation-by-visit interaction, and SHAPS score before the intervention (ie, week 0). Covariance will be specified as the unstructured structure. The treatment effects will be presented as the difference in adjusted means between the allocations at week 12 (ie, visit 12). The confidence interval will be estimated, and a *t* test will be conducted to determine the effects of treatment. The treatment effect at other weeks as well as the standardized treatment effect will also be analyzed. As a secondary outcome analysis, analysis of covariance, including baseline measures, will be conducted to test the intervention effects on SHAPS-C scores at week 12. The mixed model for repeated-measures analysis will be conducted for the other outcomes. Statistical significance will be set at *P* < .05, and all tests will be 2-tailed.

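### Enrolling 44 patients does not leave 40 after the stated 12% dropout; it leaves about 39, a minor slip inside the plan's own 32 to 72

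*Protocol article*

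**What the plan says.** The relevant figures stand close together in the Sample Size section of the protocol article. A method for sizing pilot trials gives a range: "Using this strategy, 32 to 72 individuals are needed". The article then chooses a point in it: "Hence, a sample size of 40 is sufficient for this trial". The next sentence turns that number into an enrolment figure: "Assuming a 12% dropout rate, we included a total of 44 patients". The total of 44 is repeated under Primary Objective, and the Trial Design section fixes equal allocation: "This trial was designed with an individual-level allocation with a 1:1 ratio". The same Sample Size section mentions 3 further patients, but they belong to an external preliminary trial run before this one and do not count towards the 44.

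**The concern.** The natural reading of the two consecutive sentences is that 44 is 40 inflated for 12% loss. If so, taking 12% away from 44 should return at least 40, and it does not.

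What is at stake is mainly clarity. Two different dropout rates can be read from the same lines: the stated 12%, and the 9.1% implied by going from 44 to 40. If 5 of 44 patients dropped out (11.4%), the trial would be within its stated rate and would still end with 39, one short of the size it chose. The article says its results could inform the design of confirmatory trials. Retention is one input to sizing such trials, so the planned rate should be unambiguous.

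**Working it through.** **Inputs** (protocol article, Sample Size unless noted)
- Chosen size: 40 in total
- Assumed dropout: 12%
- Enrolled total: 44
- Required range from the pilot method: 32 to 72 in total
- Allocation: 1:1 (Trial Design)

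**1. Can 44 be reproduced?**
- Standard inflation, N/(1 - d): 40/0.88 = 45.45. This rounds up to 46, which is also even, as equal arms require.
- Common shortcut, N x (1 + d), which under-allows for loss: 40 x 1.12 = 44.8, which rounds up to 45.
- The shortcut gives 44 only if 44.8 is cut down instead of rounded up. That may be where the figure came from, but the article does not say.

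The stated 44 is therefore 2 below the standard result. The allowance is 44 - 40 = 4 patients, where 12% loss calls for 46 - 40 = 6.

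**2. What does 44 deliver?**
- Expected completers at 12% loss: 44 x 0.88 = 38.72, which is 1.28 below 40.
- Largest dropout that still leaves 40: 1 - 40/44 = 4/44 = 9.1%.
- For comparison, 46 x 0.88 = 40.48.

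**3. How likely are 40 completers?** Assume that each patient drops out independently with probability 0.12, so that completers are binomial.
- With 44 enrolled, P(at least 40) = 0.379.
- With 46 enrolled, P(at least 40) = 0.688.
- With 44 enrolled, P(fewer than 32) = 0.0015.

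The last line uses the threshold that the article itself gives as the lower end of what is needed.

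**4. Does the shortfall matter for the pilot's size?** The article does not print the formula behind 32 to 72. Assume n per arm = 2 x (z/d)^2, with z = 0.8416 (the 80th percentile of the normal distribution) and d the standardized effect.
- d = 0.3: 2 x (0.8416/0.3)^2 = 15.7, so 16 per arm and 32 in total.
- d = 0.2: 2 x (0.8416/0.2)^2 = 35.4, so 36 per arm and 72 in total.

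Both ends of the stated range are reproduced. Solving the same formula for d gives d = 0.8416 x sqrt(2/n):
- 20 per arm (40 in total): d = 0.266.
- 19.36 per arm (38.72 in total): d = 0.271.

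Both lie within the 0.2 to 0.3 that the article sets as its smallest effect of interest. In terms of precision, sqrt(40/38.72) = 1.016, so a confidence interval based on completers alone would be about 1.6% wider than with 40.

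**The case against.** The strongest reply is that nothing depends on the missing one or two patients. The article reserves the language of need for the range 32 to 72, and 40 is simply a chosen value towards the lower end of it. An expected 38.7 clears 32 by more than six patients. The 38% chance of reaching 40 is correctly computed, but it refers to a threshold that the plan does not set as a minimum.

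Completers are also not the analysed sample. The primary analysis follows intent-to-treat and uses a mixed model on SHAPS scores from eight intervention visits and week 12, so a patient who leaves partway still contributes data. The article describes the trial as exploratory, and it states no retention target or progression criterion that would turn on this figure.

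All of this stands, and it sets the size of the finding. It does not remove the inconsistency: the inputs are printed without rounding, the operation is one division, and no other section of the article accounts for the gap. That 44 is within two patients of the right answer makes the slip small; it does not make the sentence correct.

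**Conclusion.** The enrolment figure and the dropout rate do not agree. At 12% loss, 44 patients leave about 39, and 44 supports a size of 40 only up to 9.1% dropout. The gap is 1.3 expected completers, or 2 enrolled patients. This result rests only on printed figures and on reading 44 as 40 plus an allowance for dropout. The probabilities also assume independent dropout, and the effect-size comparison assumes a form for the pilot formula.

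A reader might infer that the pilot is undersized or misses its own requirement. The article does not support that: 40 is not presented as a minimum, and about 39 completers meet the stated 32 to 72. The point is a minor arithmetic correction.

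**What to change.** Keep 44 patients and restate the sentence in the Sample Size section in one of two ways:
- the 44 patients allow for about 9% dropout from a size of 40; or
- with 12% dropout, about 39 of the 44 patients are expected to complete, within the 32 to 72 required.

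The choice depends on which dropout rate the investigators actually expect. If 12% is their real expectation, the second wording is the accurate one. Any matching sentence in the full protocol should be brought into line. The cost is one corrected sentence, with no change to enrolment, randomization or analysis.
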